#### Physical fitness

Cardiorespiratory fitness will be measured with the (submaximal) Åstrand-Rhyming Indirect Test of Maximal Oxygen Uptake [82], which is performed on a bicycle ergometer. Peak oxygen uptake (l/min) will be estimated based on mean steady state, sex and power output, using a nomogramme [82], and including a correction factor for age. After correction of body weight, oxygen uptake will be expressed as peak VO_2_max (ml/kg/min). The validity of the Åstrand-Rhyming nomogramme and linear extrapolation for deriving VO_2_max has been documented previously [83], and the protocol has been used with refugees [84].

Upper-body muscle strength will be measured with the Grip Strength Test [85], by using a hydraulic hand dynamometer (Saehan, Tisselt, Belgium). Participants sit down and assume a relaxed and upright position, with an arm position at a 90° angle. Every participant has four trials, alternating between the right and left hand with a 30-s resting period between trials. Grip strength can be used as a predictor of future mental health [86], and the grip strength has been used in refugee studies [87].

#### Physical activity

Physical activity will be measured objectively with a light triaxial accelerometer device (ActiGraph® wGT3X-BT) for seven consecutive days. Evidence for the validity and reliability of this device has been published previously [88]. Participants will be instructed to wear the accelerometer around the hip. Data will be recorded at a sample rate of 30 Hertz (Hz). Analysis will be performed with ActiLife software (version 6.13.2) using raw data set to 10-s epochs. Non-wear time will be determined using the algorithm defined by Troiano [89]. Participants’ data will be considered valid if the accelerometer was worn for at least 10 h a day, on four weekdays and one weekend day [90]. Using the cut-points for adults [91], we will consider time spent sedentary, and in light, moderate and vigorous physical activities [92].

#### Cognitive function

Cognitive function will be measured with an oddball paradigm [93], the two-back test [94] and the Flanker task [95] to assess sustained attention, working memory and inhibition, respectively [96]. These computer-based cognitive tests are well recognized neuropsychological tests for assessing attention [97] and executive function [98], and have been found to be reliable tools in previous research [99–101]. In the present study, the cognitive tasks will be administered with E-Prime 3.0 (PST, USA). Separately for each test, the reaction time (on response-correct trials) and accuracy will be extracted.

#### Cardiovascular risk markers

Body weight will be measured with a digital weighing scale (BC-545; Tanita, USA) and height through a stadiometer; subsequently, the body mass index (BMI) will be calculated. The BC-545 weighing scale will also be used for bioelectrical impedance analysis to assess percentage body fat, while a flexible tape will be used to determine waist circumference.

Systolic and diastolic blood pressure will be measured after the participant has rested for 5 min while seated. Blood pressure will be measured three within 5 min with the Omron® digital blood pressure monitor. Evidence for the validity of this device has been reported previously [102].

For all (capillary) blood analyses, the participants’ finger will be pricked once to collect approximately 10 blood drops. One drop will be used for the detection of anaemia. Thus, haemoglobin levels will be measured with a HemoCue® Hb 301 system (HemoCue AB; Ängelholm, Sweden). For the assessment of blood lipids (total cholesterol, low/high-density-lipoprotein cholesterol, triglycerides) and blood glucose (HbA1c), blood samples will be analysed via the Afinion 2 analyser (Abbott, Wädenswil, Switzerland). One drop of blood will be taken up by the test strip and read by the machine. Good correspondence exists between the Abbott 2 point-of-care (PAC) analyser results and reference laboratory tests for HbA1c and lipid levels [103, 104]. To assess high sensitivity C-reactive protein (hs-CRP), 20 μm blood will be collected with a Minivette® POCT EDTA (Sarstedt AG, Nümbrecht, Germany) and analysed in a Cube-S Eurolyser device (Eurolyser Diagnostica GmbH, Salzburg, Austria). Evidence for the validity of hs-CRP assessments via the Cube-S Eurolyser has been reported in previous research [105].

### Data entry and storage

Data will be double-entered, checked and merged into a single datafile. Data will be saved electronically. Backup files will be stored regularly on an external cloud. The personal data of the participants will be encrypted, and all the data obtained will be used exclusively for scientific research. The Greek study leaders will keep records in locked cupboards, and after 10 years, these records will be destroyed. Blood samples (10 drops per measurement occasion) will be collected and disposed of properly upon completion of all required assays. Since point-of-care analyses are used to examine blood data, all analyses will be carried out directly on site. Therefore, no storage of biological specimens will be needed in the current trial or for future use in ancillary studies.

### Analysis of quantitative data

#### Inspection of raw data

Data will be first inspected for missing values. Based on the nature of missingness, appropriate methods will be used to substitute missing data (see below). Data will also be screened for uni- and multivariate outliers, the latter using the Mahalanobis distance criterion. Appropriate methods to deal with uni- and multivariate outliers will be applied (replacement, transformation and/or exclusion) [106]. Before presenting the descriptive statistics, the distribution of the variables will be tested with Kolmogorov-Smirnov and Shapiro-Wilk tests.

#### Baseline differences between IG and WLCG

Prior to regular analyses of main effects, baseline differences between IG and WLCG will be explored to determine (a) whether all prerequisites are met to perform these effect analyses and (b) potential confounders and covariates.

#### Effects of the intervention

Multilevel modelling will be used to evaluate the effects of the intervention. The longitudinal analyses will be performed with linear mixed models (random effects). The within-person parameters (intercepts and slopes of outcome variables) at Level 1 will be conceptualized as dependent variables in Level 2 (between-person). Treatment conditions (as well as potential covariates) will be integrated as Level 2 predictor(s) to detect and explain between-person change over time [107]. In case of potential violation of prerequisites (e.g. non-normality of data) mixed logistic regression models will be applied.

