**Fig. 2 Fig2:**
[figure not shown]
SPIRIT figure, providing an overview of timepoints, interventions and assessments of the planned pragmatic randomized controlled trial. *Notes.* *Wait-list control group only

This trial will be a pragmatic trial, carried out in a hosting site for refugees. The pragmatic design ensures increased external validity by replicating routine practice conditions including “real-life” settings and minimum exclusion criteria [27]. Also, a pragmatic design suggests that when therapist or participant blinding is not possible, such as in exercise or psychotherapy trials, it cannot be seen as a severe flaw because routine practice is also not blinded [28]. In particular, trials with blinded interventions cannot be considered fully pragmatic [29]. Moreover, collateral therapeutic interventions derived from treatment as usual conditions are not necessarily a bias factor in the context of pragmatic trials. Integrating a collateral intervention of this sort in a broader “complex” intervention represents what is typically seen in routine practice within a contemporary stepped collaborative care model. Accordingly, our findings from a pragmatic trial will be representative of routine practice and, thus, of increased external validity.

After an initial screening, participants will be assessed three times, at baseline (before the intervention), immediately post-intervention (after 3 months) and at follow-up (after 6 months). After the first 6-month follow-up, participants of the IG will have the choice whether they want to continue participation in the exercise/sport programme, whereas participants of the WLCG will start the 3-month intervention phase. The intervention duration is based on NICE guidelines that recommend 10–14 weeks for physical activity in adult depression treatment [30]. A further data assessment will be carried out with the WLCG to examine whether similar changes will occur as in the IG, after the WLCG has received the intervention programme. Interviews will be carried out during all intervention phases in order to continuously improve the quality of the exercise/sport programme.

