### Participants

Participants will be recruited from the “Koutsochero” refugee camp in the municipality of Larissa. Approximately 1500 residents live in this camp. In March 2020, 916 residents were aged from 16 to 59 years (62% men, 38% women). The population is diverse in terms of socio-demographic background. Most of the residents are from Syria (36%), Afghanistan (34%) and Iraq (14%), whereas the remaining 16% are from the Middle East or from the sub-Saharan region.

To estimate the minimal sample size, a power analysis was carried out using G*Power 3.1. Based on the pilot study of Knappe et al. [23], a weak-to-moderate effect can be expected on our primary outcome (PTSD symptoms; *f* = 0.19). However, in the pilot study, only males and a short-term intervention (8 weeks) were considered, and no longer-term follow-ups were carried out. Therefore, we do not know whether similarly strong effects would be found in women and whether similarly strong effects can be observed after a longer follow-up period. As a consequence, we have decided to use a slightly more conservative effect size estimate (*f* = 0.15). The mean difference in the primary outcome variable (immediately post) will be used as primary endpoint. With an α-error probability of 5%, a power of 0.8, three measurement timepoints (*r* = 0.5 between repeated measures) and four groups (one male and female IG and WLCG), a total number of 108 participants is needed. With an expected dropout rate of 25%, a total of 136 participants will be recruited (68 men, 68 women), with half of them being randomly assigned to the IG or WLCG. The expected dropout rate is based on our pilot study (16%) [23] and a meta-analysis in patients with major depression (15% in a more controlled/clinical setting) [31].

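### On its plain reading, the intercept-and-slope effect model does not estimate the declared primary endpoint, the mean difference immediately post

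*Protocol article*

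**What the plan says.** Three statements in the protocol article bear on this point.

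- **Endpoint.** The sample-size paragraph under Participants states: "The mean difference in the primary outcome variable (immediately post) will be used as primary endpoint".
- **Visits.** Study design sets three assessments: "at baseline (before the intervention), immediately post-intervention (after 3 months) and at follow-up (after 6 months").
- **Model.** Effects of the intervention states: "The longitudinal analyses will be performed with linear mixed models (random effects"). It continues: "The within-person parameters (intercepts and slopes of outcome variables) at Level 1 will be conceptualized as dependent variables in Level 2 (between-person"). Treatment conditions, and possibly covariates, "will be integrated as Level 2 predictor(s) to detect and explain between-person change over time".

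Nowhere does the article mention categorical time, a piecewise slope, a contrast at a named visit, or an analysis limited to baseline and post. It also gives no coding or centring for time.

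**The concern.** The endpoint is a difference at one visit. The model's effect parameters are a starting level and a rate of change. These can be different quantities, and with three equally spaced visits a straight-line slope depends only on the first and the last. If the slope effect is read as the treatment effect, the trial answers a 6-month question although it says it will be judged at 3 months.

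This matters most if a gain at the end of the programme does not last. The sample-size paragraph itself says that it is unknown whether effects as strong as the pilot's will be seen after a longer follow-up.

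**Working it through.** **1. The plan's own sample size.** Inputs from Participants: "With an α-error probability of 5%, a power of 0.8, three measurement timepoints", "a slightly more conservative effect size estimate (*f* = 0.15"), and r = 0.5 "between repeated measures) and four groups (one male and female IG and WLCG), a total number of 108 participants is needed". For the group-by-time interaction in a repeated-measures ANOVA:

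- λ = f²·N·m/(1 − r) = 0.0225 × 108 × 3 / 0.5 = 14.58
- df1 = (4 − 1)(3 − 1) = 6; df2 = (108 − 4)(3 − 1) = 208
- power = 0.817, and 108 is the smallest multiple of four that reaches 0.80.

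So 108 reproduces, as a 6-df test across four groups and three times. That test is not the post mean difference either. It is used for planning and does not define the mixed model.

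**2. Weights in the slope.** Times are 0, 3 and 6 months. The mean is 3, the deviations are −3, 0 and 3, and their sum of squares is 18. The slope weights are therefore −3/18, 0, 3/18 = (−1/6, 0, +1/6) per month. Generalised least squares with a random intercept and slope gave the same weights under each of four covariance settings tried, with complete data.

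**3. What the slope reports for given true arm differences at (baseline, post, follow-up).**

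| True differences | Slope effect per month | Fitted difference at post |
|---|---|---|
| (0, 1, 0) | 0 | 0.33 |
| (0, 1, 0.5) | 0.083 | 0.50 |
| (0, 1, 1) | 0.167 | 0.67 |
| (0, 0, 1) | 0.167 | 0.33 |

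The slope effect is the same for (0, 1, 1) as for (0, 0, 1), although only the first has any effect at the declared endpoint.

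**4. The intercept.** With time centred at post, the treatment effect on the intercept is the fitted difference at post. Its weights are (5/6, 1/3, −1/6) + 3 × (−1/6, 0, 1/6) = (1/3, 1/3, 1/3), the plain average of the three visit differences, baseline included.

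**5. Departures from the ideal case.**
- 25% dropout, r = 0.5, three splits of when people leave: post weight 0.007 to 0.023, against 0.155 to 0.163 for follow-up.
- Post visit at the end of the 10-week programme (about 2.3 months): mean time 2.767, sum of squares 18.33, post weight −0.467/18.33 = −0.026, against 0.176 for follow-up.

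**6. Power, as an illustration.** The documents give no standardised difference at post, so d is assumed, with a range. Unit variance, r = 0.5, complete data, two-sided 5%, normal approximation. With n per arm:
- slope test: equivalent to follow-up minus baseline, SE = √[(2/n)·2(1 − 0.5)] = √(2/n)
- post minus baseline: the same SE
- baseline-adjusted post contrast: SE = √[(2/n)(1 − 0.25)]

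The 102 analysed are 136 × 0.75, or 51 per arm. For d = 0.5 and n = 51 the SEs are 0.198, 0.198 and 0.171.

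| Analysed | d | Post, unadjusted | Post, adjusted | Slope, all kept | Slope, half kept | Slope, none kept |
|---|---|---|---|---|---|---|
| 102 | 0.30 | 33% | 42% | 33% | 12% | 5% |
| 102 | 0.42 | 56% | 69% | 56% | 19% | 5% |
| 102 | 0.50 | 71% | 83% | 71% | 24% | 5% |
| 108 | 0.42 | 59% | 71% | 59% | 19% | 5% |

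A simulation of 2,000 trials per pattern at d = 0.50 and 51 per arm agrees: slope 71%, 25% and 5%; adjusted post contrast 81% to 83%.

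**The case against.** The strongest reply is that linear time is inferred. The article speaks of slopes in the plural, and a linear mixed model is linear in its parameters, not necessarily in time. Coefficients on dummy-coded or piecewise time are also slopes in multilevel language. A random intercept with fixed arm-by-time terms can be fitted to three visits, the sample-size calculation treats time as a three-level factor, and a condensed article may leave coding to an analysis plan.

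Part of this stands: a reader might infer that the protocol commits to a straight line, and it does not say so. But no alternative coding appears in the text, and the ANOVA used for planning does not specify the mixed model. One linear slope per person remains the plain reading of person-level intercepts and slopes; a random intercept with two random piecewise slopes and a residual would not be identifiable from three visits. Nor is this only a missing detail, since the article fixes both an endpoint and a kind of effect parameter, and on that reading they do not match.

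Three further inferences go too far:
- **The post visit is ignored altogether.** The zero weight is exact only with complete data and equal spacing, and post supplies one third of the fitted difference at that visit.
- **Fading is the likely course.** The protocol says only that durability is unknown.
- **The slope costs power even if the effect lasts.** With a sustained effect, the gap between 71% and about 82% comes from baseline adjustment; an unadjusted post-minus-baseline contrast also has 71%.

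**Conclusion.** The concern holds on the plain reading. The article declares a post-visit mean difference as primary and then describes effect parameters, neither of which estimates it. The slope effect puts essentially no weight on post, and the post-centred intercept effect returns two thirds of a sustained difference and one third of one present only at post.

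The practical loss depends on the course after the programme. If the effect is sustained, the slope test has the same power as an unadjusted post contrast. If half remains at 6 months, power falls to about 12% to 25% over assumed post effects of 0.30 to 0.50 SD; if none remains, it is 5%, the false-positive rate. These figures rest on linear time, r = 0.5, complete data in 102 or 108 people, and an assumed effect size. The mismatch between endpoint and parameter depends only on the linear-time reading.

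**What to change.** Keep the linear mixed model and state its primary contrast in the analysis section or analysis plan before the outcome data are analysed:

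- code time as categorical (baseline, post, follow-up) with arm-by-time terms;
- adjust for baseline IES-R, or constrain the baseline means of the arms to be equal;
- name the IG minus WLCG difference at the post visit as the single primary contrast;
- report the 6-month contrast as secondary; a slope may stay as a secondary description.

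Naming the post contrast is what removes the mismatch. Baseline adjustment is a separate gain in precision (71% to about 82% in the illustration). If a rate of change over 6 months is what is really wanted, the endpoint statement under Participants would have to change instead.

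The cost is a few sentences. The data and software stay the same.

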### Intervention

Exercise and sport activities will be offered five times per week (60 min/session) for 10 weeks. Separate programmes will be offered for men and women. Moreover, cultural particularities of the target population will be considered during programme development. In order to increase ownership, refugee camp residents will be involved in the development of the intervention programme. To this end, we will carry out short informal interviews and organize focus group discussions in order to develop appropriate programmes for both male and female participants. Participants are asked to participate in at least two sessions per week (but encouraged to do more). Participants can choose between a range of activities. Based on the experience from the pilot study [23] where 95% of the participants were satisfied or very satisfied, activities for males could include weight and endurance training, football, volleyball or other activities depending on the needs and preferences of the participants. The programme for female participants will also consider their needs and preferences. Due to possible language barriers or inter-cultural difficulties due to multi-ethnic background of refugees, it is important that the activities are tailor made, in particular, simple, acceptable, pleasant and easy to understand and apply to meet individual, gender, age, ethnic/cultural-specific needs and preferences in the real-life (pragmatic) setting of a refugee camp with limited exercise/sport facilities. Tailor-made interventions are highlighted by international physical activity guidelines for people with mental health problems [35] and proved to provide mental health benefits in both pragmatic (real-life) and clinical settings [36].

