The PhD students will receive support from local exercise/sport coaches (at least one male, one female coach) who are responsible for the implementation of the exercise and sport sessions. Support during the data assessment will come from two data assessors and from Master’s students. We will ensure that the data assessors have skills in the main languages spoken in the camp to assist during the recruitment and completion of the survey.

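### The effect model names no sex or sex-by-treatment term, although the trial is sized, minimised and delivered by sex, and its standard error omits any correlation among intervention members who share sessions

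*Protocol article*

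**What the plan says.** **Sample size** (Participants). The G*Power calculation uses f = 0.15, three timepoints with r = 0.5, and "four groups (one male and female IG and WLCG), a total number of 108 participants is needed". The same paragraph lowers f from the pilot's 0.19, partly because "we do not know whether similarly strong effects would be found in women". The pilot was also shorter and had no longer follow-up.

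**Allocation** (Procedure). Individuals are allocated by minimisation on gender, age, time fleeing and PTSD symptom severity.

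**Delivery** (Intervention; Organization of the project). "Separate programmes will be offered for men and women", each shaped by that sex's needs and preferences. Five sessions a week are on offer, at least two are asked for, and participants choose among activities. Delivery is by "local exercise/sport coaches (at least one male, one female coach) who are responsible for the implementation of the exercise and sport sessions". Under Study design, the wait-list group starts only after the 6-month follow-up.

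**Analysis** (Effects of the intervention). Within-person intercepts and slopes are at Level 1 and persons at Level 2. "Treatment conditions (as well as potential covariates) will be integrated as Level 2 predictor(s) to detect and explain between-person change over time". No sex, arm-by-sex, coach, programme or session-group term is named. The section on baseline differences between the arms says that potential confounders and covariates are to be identified from those differences.

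**The concern.** Two features of the design do not reach the analysis.

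First, sex defines the groups used for sizing, is a minimisation factor and determines which programme a participant is offered. The model does not name it. The stated route for adding covariates is an inspection of baseline differences. Minimisation on gender exists to remove such differences, so that route would tend to leave sex out. A coefficient pooled over sex could then present an effect confined to one programme as a moderate effect for everyone, although men and women are never offered the same programme.

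Second, only intervention members train together before the 6-month follow-up. Whatever a coach or a session group adds or takes away is shared among them. A model whose top level is the person treats their outcomes as independent given the covariates. The interval for the primary outcome would then be too narrow for a reader who wants to carry the result to other coaches or camps. The article hopes for that use when it speaks of scaling up and of dissemination to other camps.

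**Working it through.** **1. What the sample size rests on.** Inputs from the Participants section: f = 0.15, k = 4 groups, m = 3 timepoints, r = 0.5, alpha 5%, power 0.8. For the repeated-measures within-between interaction:

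- lambda = f² × N × m/(1 − r) = 0.0225 × 108 × 3/0.5 = 14.58
- df1 = (k − 1)(m − 1) = 6 and df2 = (108 − 4) × 2 = 208
- power = 0.817 at N = 108 and 0.799 at N = 104

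So 108 is the first total, balanced over four groups, that reaches 0.8, and the stated figure reproduces. With k = 2 (arms only) the same formula gives 74. The 6 degrees of freedom are 2 for arm-by-time, 2 for sex-by-time and 2 for arm-by-sex-by-time. The sizing test therefore contains sex terms that the analysis section does not name. It has no allowance for clustering.

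**2. Numbers at the post visit.** 136 × 0.75 = 102, so 51 per arm and 25.5 per sex within arm.

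**3. Correlation in the intervention arm only.** The documents give no intra-group correlation (ICC), so 0.01, 0.02 and 0.05 are assumptions. With n_g members per group and equal total variance in both arms:

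- design effect in the intervention arm: DE = 1 + (n_g − 1) × ICC
- variance ratio of the arm difference: (DE + 1)/2
- ratio of true to model standard error: the square root of that
- true type I error of a nominal 5% test: 2 × [1 − Φ(1.96/SE ratio)]

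Example for n_g = 25.5 and ICC = 0.02: DE = 1 + 24.5 × 0.02 = 1.49; (1.49 + 1)/2 = 1.245; √1.245 = 1.12; type I error 7.9%.

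| Groups in the intervention arm | ICC | SE ratio | Type I error |
|---|---|---|---|
| 2 of 25.5 | 0.01 | 1.06 | 6.4% |
| 2 of 25.5 | 0.02 | 1.12 | 7.9% |
| 2 of 25.5 | 0.05 | 1.27 | 12.3% |
| 4 of 12.75 | 0.01 | 1.03 | 5.7% |
| 4 of 12.75 | 0.02 | 1.06 | 6.4% |
| 4 of 12.75 | 0.05 | 1.14 | 8.5% |
| any | 0 | 1.00 | 5.0% |

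With 108 completers (two groups of 27) the ratios are 1.06, 1.12 and 1.28.

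**4. Precision of sex-specific estimates.** Assume adjustment for a baseline that correlates 0.5 with the post value (the plan's r), so the residual variance is 1 − 0.25 = 0.75 in SD² units. The 95% half-width is 1.96 × √(2/n × 0.75).

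- n = 25.5 per arm within one sex: 0.48 SD
- n = 51 per arm, both sexes: 0.34 SD

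The average of two independent sex-specific differences has standard error √(0.2425² + 0.2425²)/2 = 0.1715 SD, hence a half-width of 1.96 × 0.1715 = 0.34 SD. Averaging costs no precision when the sexes are balanced. Multiplying 0.34 by the two-group ratios 1.06, 1.12 and 1.27 gives half-widths of 0.36, 0.38 and 0.43 SD.

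**The case against.** **The analysis text is open.** It speaks of conditions and predictors in the plural and leaves covariates unspecified. A reader might infer that the model has just one treatment term, but the article does not say so, and a sex or arm-by-sex term is not excluded. Exact fixed effects are often left to a statistical analysis plan. This stands. What remains is that the article names no such term, sizes the trial on groups that need one, and gives a route to covariates that would tend to miss it.

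**The clusters are loose.** A reader might infer that each programme has its own coaches and fixed groups. The article sets a minimum of one male and one female coach and does not assign a coach to a programme. Free choice among five weekly sessions means that no stable groups are described. This stands, and it moves the likely figures towards the lower half of the table or below.

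**Individual randomisation keeps the comparison unbiased.** For an effect conditional on these coaches and programmes, person-level standard errors largely answer the question. The passages on scaling up are dissemination aims and do not claim that the interval covers other coaches. This also stands, and it is why a statement of conditional inference is a proper part of the fix.

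**The primary estimate barely moves.** With 68 men and 68 women, the average of the two differences is close to the pooled one. That is true, and it makes the change cheap. The gain is that the analysis follows the design and shows both programmes' results.

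**A smaller effect in women.** A reader might put the whole cut from f = 0.19 to 0.15 down to women and back-calculate a value for them. The article also cites the longer follow-up as a reason, so no sex-specific effect size can be derived.

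**Conclusion.** The point holds as a gap between design and analysis with a conditional loss of precision. It does not show bias in the treatment comparison.

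It rests on the text that sizing, minimisation and delivery all use sex while the effect model does not name it, and that the model's highest level is the person. How far the standard error is understated cannot be known from the documents. It is nil at an ICC of 0. Under the assumed ICCs of 0.01 to 0.05, the true standard error is about 6% to 27% above the model's with two loose groups of about 25, and about 3% to 14% above it with four groups. The type I error figures apply only if coach and group effects are regarded as draws from a wider population.

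To conclude that the primary p value will be wrong would go further than the documents allow. This is a worthwhile and inexpensive improvement to the analysis, with its main consequence in how far the result may be generalised.

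**What to change.** 1. In the IES-R model, include sex and arm-by-sex at each visit as fixed terms, whatever the baseline comparison shows. Take the simple average of the male and female intervention-minus-wait-list differences at the post visit as the primary estimate. Report both sex-specific differences with 95% intervals, and say in advance that these will be wide (about ±0.48 SD).
2. As a sensitivity analysis only, show the primary interval recalculated for assumed intervention-arm ICCs of, for example, 0.01, 0.02 and 0.05. Fit a random effect in the intervention arm only if there are enough coaches or stable session groups and these are recorded. With one coach per sex, each leading one programme, it could not be estimated. The article plans attendance lists but does not say that they record coach or session group.
3. State that the primary inference is conditional on these coaches and programmes.

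The cost is a few lines of analysis wording. Items 1 and 3 and the recalculated intervals need no new data. A random effect would need coach or session group to be recorded. The price is a wider sensitivity interval and sex-specific intervals that will often be inconclusive.
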